**Table 8.4: Solicited Systemic Reactions: Definitions, Terminology and Severity Scales For Subjects Aged  $\geq 2$  years**

|                         | Fever                                                                                                                                                                       | Headache                                                                                                                                                | Malaise                                                                                                                                                                                                                                            | Myalgia                                                                                                                                                                                                                                                                                                                                                                                                  | Shivering                                                                                                                                               |
|-------------------------|------------------------------------------------------------------------------------------------------------------------------------------------------------------------------------|----------------------------------------------------------------------------------------------------------------------------------------------------------------|-----------------------------------------------------------------------------------------------------------------------------------------------------------------------------------------------------------------------------------------------------------|-----------------------------------------------------------------------------------------------------------------------------------------------------------------------------------------------------------------------------------------------------------------------------------------------------------------------------------------------------------------------------------------------------------------|----------------------------------------------------------------------------------------------------------------------------------------------------------------|
| Diary Card term* | Temperature                                                                                                                                                                        | Headache                                                                                                                                                       | Feeling unwell                                                                                                                                                                                                                                            | Muscle aches and pains                                                                                                                                                                                                                                                                                                                                                                                          | Shivering                                                                                                                                                      |
| Definition       | Fever is defined by an axillary temperature of $\geq 37.4^{\circ}\text{C}$                                                                                                         | A headache is pain or discomfort in the head, or scalp. Does not include migraine.                                                                             | General ill feeling
Malaise is a generalized feeling of discomfort, illness, or lack of well-being that can be associated with a disease state. It can be accompanied by a sensation of exhaustion or inadequate energy to accomplish usual activities | Muscle aches and pains are common and can involve more than one muscle at the same time. Muscle pain can also involve the soft tissues that surround muscles. These structures, which are often referred to as connective tissues, include ligaments, tendons, and fascia (thick bands of tendons).

Does not apply to muscle pain at the injection site which should be reported as injection site pain. | Cold feeling                                                                                                                                                   |
| Severity scale†  | Mild
$\geq 37.4^{\circ}\text{C} - 37.9^{\circ}\text{C}$ Oral

Moderate $\geq 38^{\circ}\text{C} - 38.9^{\circ}\text{C}$ Oral

Severe $\geq 39^{\circ}\text{C}$ Oral | Mild
Noticeable but does not interfere with daily activities

Moderate
Interferes with daily activities

Severe
Prevents daily activities | Mild
Noticeable but does not interfere with daily activities

Moderate
Interferes with daily activities

Severe
Prevents daily activities                                                                                            | Mild
Noticeable but does not interfere with daily activities

Moderate
Interferes with daily activities

Severe
Prevents daily activities                                                                                                                                                                                                                                                  | Mild
Noticeable but does not interfere with daily activities

Moderate
Interferes with daily activities

Severe
Prevents daily activities |

\* These terms are the ones that will appear in the safety DC

† For fever, this information is provided for information only. The classification as mild moderate or severe will be done by the Sponsor's statistical department. The maximum daily body temperature will be recorded in the DC and then in the CRF. Severity scales for the other reactions will be provided in the DC and CRF for ease of reference.

### ***Important notes for the accurate assessment of fever***

Fever is defined, clinically, as a rectal temperature of 38.0°C or more. However for practical reasons, fever will be defined in this trial as axillary temperature of 37.4°C or more. Tympanic thermometry must not be used.

Whatever the route used, the Investigator will record in the CRF the temperature measured **without** applying any conversion factor. The CRF and the DC will provide the possibility to specify the temperature measurement route used in case it is not the requested route. Temperature should be measured once per day, at the same time each day preferably in the evening, and at the time of any apparent fever. The highest observed daily temperature should be recorded in the DC.

For the statistical analysis, results will be presented as rectal equivalent temperature. The following relationship will be used for the conversion:

$$\text{Rectal temperature} = \text{Axillary temperature} + 0.6^{\circ}\text{C}$$

### **8.3.3.3 Adverse Events from D0 to D21 after each Vaccination**

Subjects will also be instructed to record any other medical events that may occur between D0 and D21 after each vaccination. Space will be provided in the DC for this purpose. For each event, the following will be recorded:

- Start and stop dates.
- Severity of the event according to the following scale:
  - Mild: Noticeable but does not interfere with daily activities.
  - Moderate: Interferes with daily activities.
  - Severe: Prevents daily activities.
- Action taken for each event, if any (medication etc).

AEs likely to be related to the product (or to the experimenta), whether serious or not, which persist at the end of the trial will be followed up by the Investigator until their complete disappearance or the stabilization of the subject's condition. The Investigator will inform the Sponsor of the date of final disappearance of the AE and will document it on a CRF data correction sheet.

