***Unsolicited AE / ADR***

An unsolicited AE is an observed AE that does not fulfill the conditions prelisted in the CRF in terms of symptom and/or onset post-vaccination, e.g., if headache between day 0 and day 7 is a solicited event (i.e., prelisted in the CRF), then a headache starting on day 7 is a solicited event, whereas headache starting on day 8 post-vaccination is an unsolicited event.

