### **8.3.3.2 Reactogenicity (Solicited Reactions from D0 to D7 after each Vaccination)**

After vaccination, the subjects will be provided with a safety DC, a digital thermometer and a flexible centimeter ruler and will be instructed how to record the following items in the safety DC on the day of vaccination and daily for the next 7 days (i.e. D0 to D7).

- Maximum daily axillary temperature.
- Maximum daily measurement or maximum severity grade of all other solicited injection site or systemic reactions.
- Date of last day of presence of the reaction if it lasted beyond D7.
- Action taken for each event, if any (medication etc).

Tables 8.1, 8.2, 8.3 and 8.4 present the injection site and systemic reactions that will be pre-listed in the safety DCs and CRFs, together with the severity scales for subjects aged <2 years and subjects aged  $\geq 2$  years.

The D0 to D7 safety data following the two primary series vaccinations will be collected and reviewed at V02 and V04, 8 days after the vaccination. These data will be reviewed for Groups 1 and 2 by the Sponsor prior to progression to the next age group (Groups 2 and 3, respectively).

**Table 8.1: Solicited Injection Site Reactions: Definitions, Terminology and Severity Scales for Subjects Aged 6 months to <2 years**

|                         | Injection site tenderness                                                                                                                                                                                        | Injection site erythema                                        | Injection site swelling                                                                                                                                                                                                                                                                                                       | Injection site induration                                                                                                                                                                                                                                  |

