| Definition       | See severity scale                                                                                                                                                                                                      | Presence of a redness including the approximate point of needle entry | Swelling at or near the injection site

Swelling or edema is caused by a fluid infiltration in tissue or cavity and, depending on the space available for the fluid to disperse, swelling may be either soft (typically) or firm (less typical) to touch and thus can be best described by looking at the size of the swelling | Hardening at or near the injection site

Hardening is caused by a slow diffusion of the product in the tissue leading to a thick or hard area to touch at or near the injection site and thus can be best described by looking at the size of the hardening |
| Severity scale†  | Mild: minor reaction when injection site is touched

Moderate: cries and protests when injection site is touched

Severe: cries when injected limb is moved or the movement of the injected limb is reduced | Mild: <2.5 cm
Moderate: ≥2.5 to <5
Severe ≥5 cm                 | Mild: <2.5 cm
Moderate: ≥2.5 to <5 cm
Severe: ≥5 cm                                                                                                                                                                                                                                                                            | Mild: < 2.5 cm
Moderate: ≥2.5 to <5
Severe ≥5 cm                                                                                                                                                                                                            |

\* These terms are the ones that will appear in the safety DC.

† For redness and swelling, this information is provided for information only. The classification as mild, moderate or severe will be done by the Sponsor's statistical department. The maximum daily measurement of the reaction will be reported in the safety DC and then in the CRF. The severity scale for the tenderness will be provided in the diary card and CRF for ease of reference.

**Table 8.2: Solicited Injection Site Reactions: Definitions, Terminology and Severity Scales for Subjects Aged  $\geq 2$  years**

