#### 11.1.1.2 Safety Analysis

The safety analysis will report the occurrence of solicited reactions and the incidence of unsolicited events over the safety observation period by vaccine formulation and by age group. The safety observation period is 21 days after each vaccination, and 7 days after each vaccination for the solicited reactions.

In order to avoid any under-estimation of the incidences, the number of subjects with documented safety will be used as denominator of the frequencies. For solicited reactions, safety summary parameters and EMEA safety criteria, 95% CIs of point estimates of proportion will be calculated using the exact binomial distribution (Clopper-Pearson method) for proportions (23).

***Safety combined for the 21 days after the first two vaccinations and after each separate vaccination (including booster):***

The analyses of safety will address the number and percentage of subjects, by vaccine formulation and by age group, experiencing injection site or systemic AEs until 21 days after each injection (solicited reactions from D0 to D7 and unsolicited AEs/reactions until D21).

The number and percentage of subjects experiencing the following will be described by vaccine formulation and by age group:

- Each solicited and unsolicited (MedDRA preferred term) reaction or event after each injection.
- Each solicited reaction (from 0 to 7 days) after each injection according to severity, time to onset, and number of days of occurrence.
- Each unsolicited adverse reaction (MedDRA preferred term) (until 21 days) after each injection according to severity, time to onset, and duration.

(Specific solicited reactions for each age group will be presented separately).

Additionally, for subjects aged  $\geq 2$  years, the number and percentage of subjects experiencing the following reactions (MedDRA Preferred Terms) in the 3 days following each injection will be reported by vaccine and age group after each injection (as defined in the Note for Guidance on Harmonization Requirements for Influenza Vaccines [CPMP/BWP/214/96]):

- Injection site induration  $>5$  cm observed for more than 3 days.
- Injection site ecchymosis (hemorrhage).

- Pyrexia: rectal equivalent temperature  $>38^{\circ}\text{C}$  for  $\geq 24$  hours (pyrexia).
- Malaise.
- Shivering (chills).

The number and percentage of subjects in each group experiencing SAEs will be collected throughout the study.

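### The severity scale for measurable pre-listed reactions changes from size or temperature to functional impact when onset is on day 8 or later, and no measurement is listed for collection

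*Protocol*

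**What the plan says.** Section 8.3.3.2 has solicited reactions recorded "on the day of vaccination and daily for the next 7 days (i.e. D0 to D7"). Tables 8.1 and 8.2 grade erythema, swelling and induration by diameter: mild below 2.5 cm, moderate from 2.5 cm to below 5 cm, severe from 5 cm. Table 8.2, for children of 2 years and over, adds ecchymosis on the same scale; Table 8.1, for younger children, does not list it. Tables 8.3 and 8.4 grade fever by temperature, severe from 39°C. For these measured reactions the family reports the measurement, and "The classification as mild, moderate or severe will be done by the Sponsor's statistical department".

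Section 8.3.1 sets the boundary: "An unsolicited AE is an observed AE that does not fulfill the conditions prelisted in the CRF in terms of symptom and/or onset post-vaccination". Its example treats a headache that starts on day 7 as solicited, "whereas headache starting on day 8 post-vaccination is an unsolicited event".

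Section 8.3.3.3 then covers everything else: "Subjects will also be instructed to record any other medical events that may occur between D0 and D21 after each vaccination". Its only severity scale is functional, starting from "Mild: Noticeable but does not interfere with daily activities" and rising through interference to prevention of activities. The recorded items are the dates, this severity grade and the action taken.

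Section 11.1.1.2 tabulates "Each unsolicited adverse reaction (MedDRA preferred term) (until 21 days) after each injection according to severity, time to onset, and duration". Severity of unsolicited events is also a listed endpoint in sections 2.1 and 8.3.2.

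**The concern.** Two rules that are each reasonable combine badly. The onset rule moves a reaction out of the solicited class, and the change of class moves it to a scale that measures something else. Nothing in the protocol carries the cm or °C thresholds across. A reader of the unsolicited table would see grades for swelling or fever that do not mean what the same grades mean in the solicited table.

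The grade may also be hard to recover. For solicited reactions the sponsor derives it from a recorded number. For the same reaction from D8, section 8.3.3.3 lists no number from which to derive it, so a later analysis plan could not be relied on to re-grade. In an open trial, this also replaces a measurement with a judgement.

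Late local reactions always reach this output, because a footnote in section 8.3.1 treats all injection-site events as related to vaccination. Late fever enters the unsolicited-reaction line only if judged related.

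**Working it through.** The protocol gives no figure on this point, so the check applies its rules to the same event on either side of each boundary.

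**Onset boundary.** Inputs: the cm scale (Tables 8.1 and 8.2), the °C scale (Tables 8.3 and 8.4), the D7/D8 rule (section 8.3.1) and the functional scale (section 8.3.3.3).

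| Event | Onset D7, any interference | Onset D8, no interference | Onset D8, interferes | Onset D8, prevents activity |
|---|---|---|---|---|
| Swelling 6 cm | severe (6 ≥ 5) | mild | moderate | severe |
| Swelling 2 cm | mild (2 < 2.5) | mild | moderate | severe |
| 39.5°C measured by axilla | severe (39.5 ≥ 39) | mild | moderate | severe |
| 39.5°C rectal equivalent (axillary 39.5 − 0.6 = 38.9°C) | moderate, if the scale is applied to the axillary reading | mild | moderate | severe |

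The shift can be two grades in either direction: severe to mild for a large swelling that does not disturb the child, mild to severe for a small one that stops activity.

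The fever rows carry a caveat that the swelling rows do not. Table 8.4 defines fever by axillary temperature but labels its grades by another route ("Severe $\geq 39^{\circ}\text{C}$ Oral"). Section 8.3.3.2 says results will be presented as rectal equivalents (axillary + 0.6°C) without saying whether grading comes before or after conversion.

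**Age boundary.** Group 3 runs from 6 to 35 months, so it straddles the 2-year cut between Tables 8.1 and 8.2. A 5 cm bruise with onset on D0 to D7 is solicited and severe in a child of 24 months. In a child of 23 months it is not pre-listed, so it is unsolicited and can be mild, moderate or severe according to interference alone. From D8 both children are on the functional scale.

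**Reach.** The onset mismatch applies to D8 to D21, which is 21 − 8 + 1 = 14 of the 21 − 0 + 1 = 22 diary days after each injection. This counts days, not expected events. A reaction that starts by D7 and persists stays solicited.

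**Terms not affected.** Headache, malaise, myalgia and shivering in Table 8.4 already use the functional wording, so their scale does not change at D8. Section 8.3.1's own headache example therefore shows no mismatch.

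**The case against.** The strongest reply is that no planned output becomes wrong. Section 11.1.1.2 reports solicited and unsolicited severity on separate lines and presents age-specific solicited reactions separately, so no table compares grades across D7/D8 or across 2 years. That stands: there is no pooling error. It does not remove the inconsistency inside the unsolicited table, where a measurable reaction carries a grade unrelated to its size.

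Second, measurements may exist in practice. Section 10.1 describes diaries kept from D0 to D21 and rulers for injection-site reactions. Section 8.3.3.2 asks for temperature at any apparent fever. Section 8.3.3.4 has the investigator transcribe relevant data under CRF instructions that are not shown. This partly stands: some sizes and temperatures may reach the source documents. But the one section that lists what is recorded for these events names neither.

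Third, leaving ecchymosis off the list under 2 years looks deliberate, since section 11.1.1.2 limits the guideline safety criteria to children of 2 years and over. Accepted as a choice of what to solicit. It does not explain why a bruise that is reported should be graded differently within one group.

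Fourth, late events may be few. Section 1.2 says most reactions in the adult study appeared on the day after vaccination and resolved within 3 days. This stands and limits the importance of the point.

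A reader might also infer that the rule hides late reactions to the aluminum adjuvant, because section 1.2 mentions subcutaneous nodules. The documents do not support that. Section 1.2 does not describe nodules as late, nodule is not a term in Tables 8.1 to 8.4, and the change of scale can raise a grade as well as lower it.

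**Conclusion.** The point holds as an inconsistency of severity grading. Measurable pre-listed reactions are graded by size or temperature with onset up to D7 and by function with onset on D8 to D21, and bruising on D0 to D7 has the same split at 2 years within Group 3. The swelling and bruising examples follow directly from the text. The fever example depends on which route the thresholds refer to.

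The possible shift is up to two grades in either direction for an affected child. How many children would be affected cannot be estimated: the protocol gives no incidence for late-onset reactions, nor for how often a large one leaves activity undisturbed. A reader might infer that severe rates will be understated by some amount; the documents support neither a direction nor a size.

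A reader might also infer that the step-down decisions are compromised. They are not: the review described in sections 5.1.2 and 5.2 uses D0 to D7 data and focuses on severe fever and SAEs. The point merits a short amendment and does not undermine any planned analysis.

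**What to change.** In section 8.3.3.3, add three statements.

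1. An unsolicited event that is a measurable term (erythema, swelling, induration, ecchymosis, fever) in the solicited table for the subject's own age band is graded on that table's scale, whatever its onset day.
2. Injection-site ecchymosis in children under 2 years is graded on the cm scale of Table 8.2.
3. The maximum size, or the maximum temperature with its route, is recorded in the AE table, and the sponsor derives the grade as it does for solicited reactions.

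Keep the functional scale for all other terms. Tying the rule to the child's own age band and to measured terms keeps infant scales, such as those for appetite or irritability, from being applied to older children. Recording the route does not settle the oral and axillary wording in Table 8.4; that must be reconciled separately.

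The cost is a short insertion, one extra CRF field and slightly more data entry. Families already receive a ruler and a thermometer.
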